### Primary outcome

The primary outcome is the difference in the incidence of PTSD between the two groups at 1 month postoperatively, assessed using the Clinician-Administered PTSD Scale for DSM-5 (CAPS-5). The CAPS-5 is a structured diagnostic interview widely regarded as the gold standard for PTSD assessment. Neuropsychological evaluations will be conducted by professionally trained anesthesiologists who are blinded to group allocation and will perform assessments in a calm and controlled environment. Data analysts will also remain blinded to treatment assignments. The CAPS-5 provides both a diagnostic determination (presence or absence of PTSD) and a continuous measure of PTSD severity, including the four core symptom clusters: intrusions, avoidance, negative alterations in cognition and mood, and arousal/reactivity. The assessment can be administered by appropriately trained clinicians or paraprofessionals.

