### Randomization and blinding

An independent research staff member will generate the randomization sequence using the Sealed Envelope online tool,^1^ with a 1:1 allocation ratio, permuted blocks of 2 and 4, and stratification by age (18–64 and ≥65 years). The allocation results will be stored in sequentially numbered, sealed opaque envelopes. Patients will be randomly assigned to either the SGB group or the control group (*n* = 150 per arm). The anesthesiologists responsible for administering the intervention will be aware of group allocation due to the nature of the procedure but will not be involved in patient recruitment, data collection, or outcome assessment. Patients, surgeons, postoperative care providers, outcome assessors, and the data analyst will remain blinded to group assignments throughout the study. Successful stellate ganglion block in the intervention group will be confirmed by the occurrence of Horner’s syndrome (ptosis, miosis, enophthalmos, conjunctival hyperemia, and facial anhidrosis). Patients will not be informed whether these clinical signs occur, thereby maintaining the integrity of blinding. The schedule for patient enrollment, study interventions, and outcome assessments will adhere to the SPIRIT statement (Table 1).

**Table 1 tab1:** SPIRIT schedule of patient enrolment, study interventions and outcome assessment.

Time point	Study period									
	Enrolment	Allocation	Post-allocation					Close-out	Follow-up	
	Emergency room	15 min Pre-an	Intraoperative	Post-op	24 h Post-op	48 h Post-op	72 h post-op	Discharged	1 month	6 months
Patient enrolment										
Eligibility criteria	**×**									
Written informed consent	**×**									
Demographic data	**×**									
Baseline characteristics	**×**									
Randomization/allocation	**×**									
Study interventions										
SGB		**×**								
Sham SGB		**×**								
Outcome assessment										
CAPS-5 score									**×**	**×**
BAI score					**×**	**×**	**×**			
VAS Sleep score					**×**	**×**	**×**			
NRS Pain score					**×**	**×**	**×**			
HRV			**×**		**×**	**×**				
Recovery time				**×**						
Extubation time				**×**						
RASS score				**×**						
Length of hospital stay								**×**		
Safety Outcomes										
Neck pain			**×**		**×**	**×**	**×**			
Dizziness			**×**		**×**	**×**	**×**			
Tinnitus			**×**		**×**	**×**	**×**			
Dyspnea			**×**		**×**	**×**	**×**			
Anaphylaxis			**×**		**×**	**×**	**×**			
Sinus bradycardia			**×**		**×**	**×**	**×**			

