### Sample size calculation

According to the literature, the incidence of PTSD at 1 month after trauma surgery is approximately 23.2% (21). Previous epidemiological studies have reported rates up to 30–33% in patients with ocular trauma, substantially higher than in the general trauma population (9, 11). Based on these data and our small pilot observation, we set the expected PTSD incidence in the control group at 26%. We therefore adopted 26% as a conservative estimate to guide the sample size calculation. This conservative approach ensures that statistical power will not be underestimated if the true incidence in our study population is somewhat lower than that reported in epidemiological studies, while still remaining consistent with the published range. We hypothesize that SGB will reduce the risk of postoperative PTSD by 50% in patients undergoing emergency ocular trauma procedures. Using a two-sided test with a significance level of *α* = 0.05 and 80% power, a minimum of 142 participants per group is required. Accounting for an anticipated 10% dropout rate, the final target sample size is 300 patients, with 150 allocated to each group.

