### Statistical analysis

The normality of continuous variables will be evaluated using the Shapiro–Wilk test. Data following a normal distribution will be reported as mean (standard deviation, SD), while non-normally distributed data will be expressed as median (interquartile range, IQR). Group comparisons for normally distributed continuous variables will be conducted using independent t-tests or repeated measures ANOVA, as appropriate. For non-normally distributed variables, analyses will be performed using the Mann–Whitney U test or generalized estimating equations (GEE) to account for repeated measures and potential correlations. Categorical data will be presented as counts (percentages) and analyzed using the chi-square test or Fisher’s exact test, as appropriate, based on expected frequency distributions.

The 1-month postoperative prevalence of PTSD, defined as the primary endpoint, will be compared between groups using the chi-square (*χ*^2^) test. Group differences will be reported as odds ratios (ORs) with 95% confidence intervals (CIs). To control for potential confounders, logistic regression models will be used to obtain adjusted ORs. Subgroup analyses will also be conducted using logistic regression to examine treatment-by-covariate interactions.

Analyses of the primary outcome will primarily follow a modified intention-to-treat (mITT) approach, including all randomized participants with available data, regardless of protocol adherence. A per-protocol (PP) analysis will also be performed, excluding patients with major protocol deviations or who withdrew consent, to assess the treatment effect among fully adherent participants. No multiple testing correction is planned for secondary outcomes; these results will be interpreted as exploratory.

To evaluate CAPS-5 score changes over time (at 1- and 6-month follow-ups), repeated measures analysis will be performed using a covariate-adjusted linear mixed model (LMM). Fixed effects will include group (SGB vs. control), time (1 month vs. 6 months), and the group-by-time interaction. Potential confounding variables—such as sex, age, Injury Severity Score (ISS), laterality of ocular trauma (unilateral or bilateral), time from injury to surgery, and baseline VAS pain scores—will be entered as covariates. If significant time-by-covariate interactions are detected, they will be incorporated into the model. Results will be presented as least squares means (LSMs) with 95% CIs.

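### The primary test leaves out the randomised age stratum, and the odds ratio, its only effect measure, is not on the scale of the stated outcome and hypothesis

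*Protocol article*

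**What the plan says.** - **Design.** Randomization and blinding sets a 1:1 allocation with "stratification by age (18–64 and ≥65 years"). The trial has two hospitals, but centre is not a stratification factor.
- **Outcome.** Primary outcome: "The primary outcome is the difference in the incidence of PTSD between the two groups at 1 month postoperatively".
- **Hypothesis.** Sample size calculation sets the control rate at 26% and supposes that "SGB will reduce the risk of postoperative PTSD by 50" per cent, that is, to 13%. With a two-sided alpha of 0.05 it then states: "80% power, a minimum of 142 participants per group is required".
- **Primary analysis.** Statistical analysis: "The 1-month postoperative prevalence of PTSD, defined as the primary endpoint, will be compared between groups using the chi-square" test. The next sentence fixes the effect measure: "Group differences will be reported as odds ratios (ORs) with 95% confidence intervals (CIs").
- **Adjustment.** A logistic model follows and gives adjusted odds ratios for confounders that are not named there. Further covariate-adjusted models are listed as sensitivity analyses. Age is named as a covariate only for the CAPS-5 mixed model, in a list given as examples.

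The article plans neither a risk difference nor a risk ratio for the primary outcome.

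**The concern.** This is not about detail left to an unseen analysis plan: the article itself names the primary test and the effect measure. Two things do not fit the rest of the design.

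First, age was thought important enough to stratify the randomisation, but the test that decides the trial does not use it. Stratified allocation removes chance imbalance in age between the arms. An unstratified test still counts the between-age variation as noise.

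Second, outcome and hypothesis are stated in risks, while the result is to be reported in odds. At a control rate near 26% the two differ visibly, so the reported estimate and its interval do not show directly whether risk was halved. The plan also sets crude and adjusted odds ratios side by side. The odds ratio is non-collapsible, so the two can differ even with perfectly balanced arms, and a reader may take that gap for confounding.

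**Working it through.** **Inputs from the protocol.** Control rate 0.26; risk halved, so 0.13 on treatment; two-sided alpha 0.05; power 0.80; 142 per group required; 150 per group enrolled; 10% dropout; age strata 18–64 and ≥65.

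**1. The plan's own figure.** Two proportions, unpooled variance:

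n = (1.960 + 0.842)² × [0.26 × 0.74 + 0.13 × 0.87] / (0.26 − 0.13)² = 7.849 × 0.3055 / 0.0169 = 141.9, so **142 per group**, as stated. (The pooled-variance version gives 145.) The sample size is thus an unstratified calculation on the risk-difference scale.

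**2. The planned effect on three scales.**
- Risk difference: 0.26 − 0.13 = 0.13.
- Risk ratio: 0.13 / 0.26 = 0.50.
- Odds ratio: (0.13/0.87) / (0.26/0.74) = 0.1494 / 0.3514 = **0.425**, a 57% reduction in odds.

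**3. The reverse.** An odds ratio of 0.50 at 26% control gives treated odds 0.50 × 0.3514 = 0.1757. The risk is 0.1757 / 1.1757 = 14.9% and the risk ratio 0.149 / 0.26 = **0.575**. This looks like the hypothesised halving but falls short of it.

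**4. Dependence on the control rate.** Hold the risk ratio at 0.50 and vary the control rate over the range the protocol cites. The odds ratio is 0.434 at 23.2%, 0.425 at 26%, 0.412 at 30% and 0.401 at 33%. One and the same risk reduction gives different odds ratios.

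**5. Cost of ignoring the age stratum.** The documents give neither the share of older patients nor age-specific rates, so both are assumed, with about 26% overall. Each scenario used 400,000 simulated trials with arms balanced within stratum. Type I error was simulated with 270 analysed (2 × 135), and power with a risk ratio of 0.50 in both strata. Entries are chi-square / Cochran-Mantel-Haenszel (CMH), in per cent.

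| Share ≥65 | Control rate 18–64 / ≥65 | Type I error, 270 | Power, 284 | Power, 270 |
|---|---|---|---|---|
| 10% | 27 / 17 | 5.07 / 5.00 | 79.98 / 80.04 | 78.27 / 78.09 |
| 15% | 28 / 14.7 | 4.96 / 4.98 | 79.99 / 80.16 | 78.15 / 78.11 |
| 20% | 30 / 10 | 4.75 / 4.99 | 80.17 / 80.75 | 78.46 / 78.85 |
| 30% | 33 / 9.7 | 4.44 / 5.01 | 80.39 / 81.47 | 78.66 / 79.62 |
| 20% | 20 / 50 | 4.21 / 4.94 | 80.37 / 81.78 | 78.59 / 79.86 |
| 20% | 26 / 26 | 5.12 / 4.97 | 79.91 / 79.92 | 77.98 / 77.66 |

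The largest gain is 81.78 − 80.37 = 1.4 points. With little or no age effect, CMH gains nothing and can be about 0.3 points lower.

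A hand check of the fifth row: pooled variance 0.26 × 0.74 = 0.1924; within-stratum variance 0.8 × 0.20 × 0.80 + 0.2 × 0.50 × 0.50 = 0.178; √(0.178/0.1924) = 0.962. The effective cut-off is 1.960 / 0.962 = 2.04, a two-sided level of about 4.2%, which agrees with the simulation.

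**6. Room for covariates.** With 150 × 0.9 = 135 analysed per arm, expected events are 135 × (0.26 + 0.13) = 52.7, about **53**. Treatment, age stratum, centre, sex, Injury Severity Score, laterality, time from injury and baseline pain make eight parameters: 53 / 8 = 6.6 events each. Treatment, age stratum and two covariates make four: 53 / 4 = 13 each.

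**The case against.** The strongest reply is that nothing here is invalid. The chi-square tests a difference in proportions, which is what the outcome definition asks for, and it matches the sample-size formula. Adjusted odds ratios are planned as well. Categorical data will be shown as counts and percentages, so a reader can work out the risk difference and risk ratio. Covariate lists and extra effect measures may stand in the analysis plan that the protocol mentions.

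Much of this stands. The test is sound, and adjustment is not absent. But counts only let a reader derive a crude interval; they do not make an interval on the scale of the hypothesis part of the pre-specified result, nor one that respects the stratification. And the article does not leave the effect measure open: it names the odds ratio.

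Stronger readings are tempting, and the documents do not support them:

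- **That the unstratified test risks a false positive.** Type I error was 4.2% to 5.1%. When age is prognostic, the error is on the conservative side.
- **That leaving out centre departs from the randomisation.** Centre was not a stratification factor, and the covariate lists are open or absent.
- **That the unadjusted odds ratio has needlessly wide intervals.** Logistic adjustment widens the standard error of the log odds ratio. In a simulation with assumed covariates it rose from about 0.33 to 0.347–0.366. Power gains arise because the estimate moves further from 1.
- **That full adjustment would recover several points of power.** Gains of about 2 to 5 points appear in simulation only with assumed c-statistics of 0.66 to 0.74, which the documents do not give.
- **That the protocol treats the odds ratio as a risk ratio.** It does not. Misreading by others is a risk, not a statement in the text.

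**Conclusion.** The point holds as a matter of efficiency and reporting, not of validity. The scale mismatch needs only the protocol's own figures: the hypothesised halving of risk would be reported as an odds ratio of 0.425, and an odds ratio of 0.50 would mean a risk ratio of 0.575. The loss from ignoring the age stratum is small, about 0 to 1.4 points of power, and rests on assumed age shares and age-specific rates. The required sample size does not materially change. Any further gain from covariates depends on their prognostic strength, which is unknown here. The change is worth making because it is free.

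**What to change.** Before database lock, reword the primary analysis as follows.

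1. Stratify by the randomised age groups. Either use a Cochran-Mantel-Haenszel test with the common (Mantel-Haenszel) risk difference, or fit a logistic model with treatment, age and a few strong covariates named in advance, followed by standardisation to risks.
2. Report the risk difference and the risk ratio, each with a 95% confidence interval.
3. Keep the unadjusted chi-square and the odds ratio as supportive. Note that crude and adjusted odds ratios are expected to differ even without confounding.
4. Keep any covariate list short, given about 53 expected events, and state how missing covariate values are handled so that patients are not lost from the primary analysis.
5. Centre may be added as a second factor, but the randomisation does not require it.

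The cost is wording and some programming. If the named software does not offer the common risk difference, it can be computed from the stratum counts. No new data and no additional patients are needed.

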Sensitivity analyses will be conducted to evaluate the robustness of the findings. These will include complete case analysis and multiple imputation for handling missing data, additional covariate-adjusted regression models, and subgroup analyses to explore the consistency of treatment effects under different modeling assumptions.

As exploratory endpoints, Spearman’s or Pearson’s correlation analyses will be used to assess the relationships between preoperative VAS pain scores or Injury Severity Scores (ISS) and postoperative CAPS-5 scores.

All hypothesis testing will be two-sided, with a significance level of *p* < 0.05. For subgroup interaction terms, a threshold of *p* < 0.10 will be used to indicate potential effect modification. All statistical analyses will be performed using SPSS software (version 25.0; IBM Corp., Armonk, NY, United States). No interim analysis will be conducted.

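### For the primary 1-month test, the complete-case sensitivity analysis is the primary analysis again, and no named analysis varies the assumption about missing outcomes by arm

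*Protocol article*

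**What the plan says.** All from the protocol article.

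- **Endpoint** (Primary outcome): "The primary outcome is the difference in the incidence of PTSD between the two groups at 1 month postoperatively", diagnosed by CAPS-5 interview.
- **Test** (Statistical analysis): 1-month PTSD "will be compared between groups using the chi-square" test. Adjusted odds ratios from logistic regression are additional.
- **Primary set** (same section): a modified intention-to-treat set, "including all randomized participants with available data, regardless of protocol adherence".
- **Per-protocol set** (same section): formed by "excluding patients with major protocol deviations or who withdrew consent".
- **Sensitivity analyses** (same section): "These will include complete case analysis and multiple imputation for handling missing data", followed by "additional covariate-adjusted regression models, and subgroup analyses to explore the consistency of treatment effects under different modeling assumptions".
- **Expected loss** (Sample size calculation): "Accounting for an anticipated 10% dropout rate, the final target sample size is 300 patients".

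The imputation model and its missing-data assumption are not stated. A predefined statistical analysis plan is mentioned under Data collection and monitoring but is not shown.

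**The concern.** A sensitivity analysis is informative only if it changes an assumption of the primary analysis. Here the first missing-data item changes none: a patient without a 1-month diagnosis is outside the primary 2×2 table and also outside the complete-case table. If the two results were set side by side, their agreement would be an identity and not evidence of robustness.

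This matters because loss related to the outcome is plausible. The endpoint is an interview about the trauma, post-discharge information comes from interviews or telephone calls, and avoidance is one of the symptom clusters of the disorder. At the anticipated 10% loss, about 30 of 300 patients would have no primary outcome. The question is whether the named analyses could show that a conclusion depends on those patients.

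**Working it through.** **1. Are the two sets the same?** The primary test uses one binary outcome, one visit and no covariates. Being in the primary set requires a 1-month PTSD status, and so does being a complete case. The patients, table, odds ratio and p-value are therefore identical. The sets can differ in two other places: adjusted logistic models, if a covariate is missing, and the CAPS-5 mixed model, if complete means both visits. Neither difference brings back a patient whose 1-month outcome is missing.

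**2. What do the other named items do about missing outcomes?** Adjusted models and subgroup analyses use the same observed outcomes. The per-protocol set removes patients and adds none. Only multiple imputation puts missing outcomes back.

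**3. The plan's own figure.** With control rate 0.26, halved to 0.13, two-sided α 0.05 and 80% power:

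n = (1.960 + 0.842)² × (0.26×0.74 + 0.13×0.87) / 0.13² = 141.9, that is 142 per group, as stated. The planning rates are therefore 26% and 13%.

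**4. An example on those rates.** Assumption: the 10% loss falls evenly, 15 of 150 per arm, leaving 135 observed. The whole numbers nearest the planning rates are 35/135 (25.9%) for control and 18/135 (13.3%) for the stellate ganglion block (SGB) arm.

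Uncorrected chi-square: χ² = (p₁ − p₂)² / [p(1 − p)(1/n₁ + 1/n₂)], with p the pooled rate. Observed cases: χ² = 6.785, p = 0.009, OR 0.44 (95% CI 0.24 to 0.82).

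**5. Informative loss of equal strength in both arms.** Multiply the odds of PTSD among missing patients, relative to observed patients in the same arm, by a common factor. The observed odds are 18/117 and 35/100. Expected counts are rounded to whole patients, and the test is on 150 per arm.

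| Factor | Missing SGB with PTSD | Missing control with PTSD | p |
|---|---|---|---|
| 1 | 2/15 | 4/15 | 0.006 |
| 2 | 4/15 | 6/15 | 0.007 |
| 5 | 7/15 | 10/15 | 0.006 |
| 10 | 9/15 | 12/15 | 0.007 |
| 20 | 11/15 | 13/15 | 0.012 |
| all have PTSD | 15/15 | 15/15 | 0.028 |

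Significance is kept throughout.

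**6. Loss that differs by arm.** Hold missing controls at about their observed rate, 4/15, for a total of 39/150.

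- 7/15 among missing SGB patients: 25/150, p = 0.048.
- 8/15: 26/150. Pooled rate 65/300 = 0.2167; χ² = 0.0867² / (0.2167 × 0.7833 × 2/150) = 3.319; p = 0.068.

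Other tipping points:

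| Missing control with PTSD | SGB count at which p first reaches 0.05 | p |
|---|---|---|
| 0/15 | 4/15 | 0.056 |
| 2/15 | 6/15 | 0.062 |
| 3/15 | 7/15 | 0.065 |
| 4/15 | 8/15 | 0.068 |

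The extreme case, 15/15 SGB and 0/15 control, gives 33/150 versus 35/150, p = 0.78.

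**7. How strong is the asymmetry at the 4/15 and 8/15 tipping point?** In the SGB arm the odds among missing patients are (8/7)/(18/117) = 7.4 times those among observed patients. In the control arm the ratio is (4/11)/(35/100) = 1.04.

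**The case against.** Four objections have weight.

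- **The mechanism is not arm-specific.** Avoidance would keep patients with PTSD away in both arms, and patients and assessors are blinded. Step 5 shows that such loss does not overturn a result at the planned effect. This stands. A reader might infer that avoidance-driven dropout by itself threatens the conclusion; the plan's own figures do not support that. The tipping points need strongly differential loss, for which the document gives no reason.
- **Missing data are not ignored.** Multiple imputation is listed and is not redundant. It can adjust for loss explained by recorded variables such as early anxiety or pain. This stands. A reader might infer that nothing addresses informative loss; that is too strong. Missing at random is also an inference from the usual form of the method, since the document states no assumption.
- **The list is open and the analysis plan is not shown.** A tipping-point analysis may be specified there. This stands, so its absence here is not an omission from the trial's plan. The duplication does not depend on the unseen plan, because the set, the test and the list are all fixed in the article.
- **Complete-case analysis has a role for other models.** True for adjusted and repeated-measures models, and the point is limited accordingly.

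Nor does the document say how agreement between the two analyses would be reported, so a misleading claim of robustness is a risk, not a stated intention.

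**Conclusion.** For the unadjusted 1-month chi-square test, the listed complete-case analysis reproduces the primary result and carries no information about missing outcomes. This follows from the definitions and needs no numerical assumption. Of the analyses named, only multiple imputation addresses missing outcomes; in its usual form it does not examine loss that depends on the unobserved diagnosis.

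The numerical consequence is conditional. It assumes 15 missing per arm and an observed result at the planned effect. Equal informative loss then leaves p at 0.028 or below, while arm-specific loss can take it past 0.05, as at 4/15 versus 8/15 (p = 0.068). The duplication does not bias the primary estimate or alter its error rate. It leaves one of the two missing-data items without a function for the endpoint that matters most.

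**What to change.** For the primary endpoint, replace the complete-case item with one of these:

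- a two-way tipping-point table over the number of PTSD cases among missing patients in each arm, with the chi-square p-value and odds ratio in each cell; or
- delta-adjusted multiple imputation, with delta varied separately by arm.

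Varying the arms separately is essential, because a common shift did not change the conclusion in the example. Keep multiple imputation under missing at random, state that assumption, and use the 24, 48 and 72 h BAI, sleep and pain scores and the 6-month CAPS-5 as auxiliary variables. Complete-case analysis may stay for the adjusted and repeated-measures models if it is labelled as such.

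If the unshown analysis plan already contains such an analysis, it is enough to align the article's list with it. The cost is a few lines of text and a little extra programming. The variables are already scheduled in Table 1, and the primary analysis is unchanged. The change should be made before unblinding.
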